# Impact of glycemic variability on cognitive impairment, disordered eating behaviors and self-management skills in patients with type 1 diabetes: study protocol for a cross-sectional online study, the Sugar Swing study

**DOI:** 10.1186/s12902-022-01191-4

**Published:** 2022-11-18

**Keywords:** Type 1 Diabetes, Cognition, Eating Behaviors, Disordered Eating, Attention, Impulsivity, Continuous glucose monitoring, Glycemic Variability, Self-management

## Abstract

**Background:**

People living with type 1 diabetes (PWT1D) are at increased risk for impairments in brain function, which may impact on daily life. Cognitive impairments in PWT1D might contribute to increasing eating disorders, reducing self-management skills, and deteriorating glycemic control*.* Glycemic variability may be a key determinant of disordered eating behaviors, as well as of cognitive impairments. The main objective of this study is to better understand the impact of glycemic variability in disordered eating behaviors and cognitive impairment, and its consequences on self-management skills in PWT1D.

**Method:**

We aim to recruit 150 PWT1D with 50% of men and women in this cross-sectional study. Participants will record their glycemic variability over a 10-day period using a continuous glucose monitoring system (CGMS) and track their dietary intakes using image-assisted food tracking mobile application (2 days). Over four online visits, eating behaviors, diabetes self-management’s skills, anxiety disorders, depression disorder, diabetes literacy and numeracy skills, cognitive flexibility, attention deficit, level of interoception, and impulsivity behaviors will be assessed using self-reported questionnaires. Cognitive functions (i.e., attention, executive functions, impulsivity, inhibition and temporal discounting), will be measured. Finally, medical, biological and sociodemographic data will be collected. To further our understanding of the PWT1D experience and factors impacting glycemic self-management, 50 PWT1D will also participate in the qualitative phase of the protocol which consist of individual in-depth face-to-face (virtual) interviews, led by a trained investigator using a semi-structured interview.

**Discussion:**

This study will contribute to highlighting the consequences of blood sugar fluctuations (i.e., "sugar swings"), in daily life, especially how they disrupt eating behaviors and brain functioning. A better understanding of the mechanisms involved could eventually allow for early detection and management of these problems. Our study will also seek to understand the patients' point of view, which will allow the design of appropriate and meaningful recommendations.

**Trial registration:**

ClinicalTrials.gov, NCT05487534. Registered 4 August 2022.

## Background

The discovery of insulin 100 years ago deeply transformed the face of type 1 diabetes (T1D) from a rapid life-threatening disease to a chronic condition [1]. By becoming a long-term disease, T1D brings new challenges to physicians including the management of chronic complications. Prevention screening and management of classical micro- and macrovascular complications of T1D (e.g., retinopathy, nephropathy, neuropathy and cardiovascular complications) have been the focus of much research, establishing the crucial importance of the glucose control for primary and secondary prevention [2]. However, other complications of T1D such as brain impairment, that may significantly affect quality of life, are still understudied and thus, under-recognized and poorly addressed.

It has been established that T1D in children affects brain development and that impairment in brain structure and function may increase over time [3]. In elderly patients with T1D (PWT1D), almost 50% experience significant cognitive impairment [4]. In a recent study, Jacobson et al. found that adults with a long history of T1D have reduced brain gray and white matter volume [5]. They observed that the brain volumes of patients with T1D (PWT1D) appeared like those of individuals without diabetes who are 4–9 years older, and thus in relatively young elderly patients (age median: 60 yr) [5]. In elderly PWT1D, almost 50% experience significant cognitive impairment [4]. Although of excellent quality, the tests used in most studies detect cognitive problems that are already clinically perceptible [6, 7]. Less is known about “subclinical” or more specific brain function impairment, and their functional relevance. Such “subclinical” impairment may affect a higher number of PWT1D, and their impact on daily life is likely underestimated. Studies suggest that PW1TD have a specific pattern of cognitive impairment: 1) that predominantly affects global intelligence, attention, psychomotor speed, executive function and cognitive flexibility [8], 2) among executive functions, inhibition, working memory and set-shifting (i.e., the ability to alternate between one task and another) might be particularly affected [9], 3) cognitive impairment patterns and their consequences may differ by sex [10]. However, observed effect sizes were weak to mild and the literature remains scarce and inconsistent.

Diabetes self-management aiming for strict glycemic targets requires insulin therapy (e.g., multiple daily injections or insulin pump therapy) and active participation from PWT1D, and sometimes of their relatives. It has been estimated that life with T1D requires up to 180 health-related decisions per day. The most used factor to assess the severity of T1D is the HbA1c. While HbA1c accurately reflects long-term glycemic control, it only partially reflects the day-to-day variations that underlie T1DM management and dietary choices. Glycemic variability has been well studied and has emerged as a more meaningful measure of glycemic control. Based on continuous glucose monitoring, glycemic variability measurements reflect either short-term (with-day and between-day variability) or long-term blood glucose levels fluctuations (i.e., sugar swing) [11]. Higher glycemic variability has been associated with an increased risk of macro- and microvascular complications, as well as a higher mortality rate [11]. However, studies on cognitive impairments or disordered eating in patients with T1DM rarely use continuous glucose monitoring system (CGMS) and glycemic variability measurement (e.g., coefficient of variation).

Insulin restriction or omission to control weight is a well-known and frequent phenomenon, affecting up to 40% of PWT1D [12, 13]. Such behavior can culminate in a particular form of disease close to anorexia nervosa called diabulimia [13]. This disorder results in dramatic increases in hemoglobin A1c (HbA1c) levels [13]. Purging or binge eating behaviors are also frequent disordered eating behaviors (DEB) in PWT1D (associated or not with restrictive eating behaviors) [14]. Moreover, the presence of binge eating behavior seems to be associated with higher anxiety and depression levels [15]. It has been demonstrated, and even mathematically modeled, that appetite is partly controlled by glycemic levels (e.g., hypoglycemia as a hunger trigger and hyperglycemia as a hunger suppressor) [16]. However, these findings are mainly based on animal studies and the impact of glycemic variability on eating behavior, and vice versa, needs to be further studied in PWT1D. Recently, Zhou et al. found that total daily energy intake does not seem to impact the glycemic variability index in PWT1D [17]. As glycemic variability is a dynamic phenomenon over the day and between days, its impact on food behavior is not likely to be detected by a change in the total amount of food consumed. More accurate reporting of both eating behavior (including loss of control eating and binge eating behaviors) and macronutrient intake (especially carbohydrate intake) may be more relevant to evaluate the consequences of glycemic variability. Moreover, we did show that inaccurate carbohydrate counting is frequent and associated with higher daily blood glucose variability in PWT1D [18]. Thus, diabetes-related numeracy will be considered a potential confounder in our study. Treasure et al. made the assumption that DEB may result in larger glycemic fluctuations [19]. Higher glycemic fluctuations may in turn affect cognitive function, potentially leading to more difficulties to maintain adequate blood glucose levels and eating behavior, thus setting up a vicious circle. Indeed, cognitive functions are highly involved in eating behavior, as they allow the modulation of food intake [20]. We recently published a meta-analysis in which we established that binge eating disorder is significantly associated with impairments in cognitive flexibility, inhibitory control, attention, and planning [21]. Thus, some of the cognitive impairments identified in PWT1D are the same as those identified in binge eating disorder. This overlap may account for DEB occurrence in PWT1D. However, there is currently limited or no evidence of the association between cognitive impairment, DEB and glycemic variability in PWT1D. The relationship between glycemic variability and DEB is challenging to establish since it could be mediated by impairment in executive functions (especially inhibitory control) and/or in interoceptive awareness (i.e., the ability to perceive body signals). Considering such parameters as potential mediators of this relationship might provide the opportunity to address this challenge.

Current evidence also suggests that cognitive impairment may affect treatment adherence and diabetes self-management in PWT1D [22, 23], with the potential to worsen glycemic levels. Poorly controlled diabetes may in turn worsen further cognitive functions [23, 24]. Using questionnaires, but not cognitive tasks, Vloemans et al. found that poorer executive functions are associated with higher HbA1c over time in youth with T1D [25]. The underlying mechanisms responsible for cognitive impairment in PWT1D are difficult to characterize, partly due to numerous confounding factors (e.g., age, HbA1c level, psychiatric comorbidities). Chronic hyperglycemia, longer diabetes duration, and the presence of micro- and macrovascular complications have all been associated with a higher risk of cognitive impairment in PWT1D [3]. Severe and/or repeated hypoglycemia episodes might also be involved in the increased risk of dementia in PWT1D [26]. While most studies focused on acute hypoglycemia, few have assessed glycemic variability, which better considers the broad spectrum of hyper/hypoglycemia frequency, intensity and duration. Another key limitation in current literature is the lack of reporting either hypoglycemia or hyperglycemia episodes during testing, even though it can have a direct effect on performance [24]. These limitations will be addressed in the present study. Based on the SEARCH cohort, Nip et al. were the first to explore the association between insulin sensitivity (insulin sensitivity score estimated from clinical measures including waist circumference, HbA1c, and triglyceride levels) and DEB. In PWT1D, they found that the presence of DEB was associated with greater insulin resistance and a higher body mass index (BMI) [27]. In patients with obesity, we have shown that higher dysfunctional adipose tissue is associated with greater insulin resistance and a higher severity of binge eating behaviors [28]. Hence, accounting for insulin resistance as a potential mediator of the association between glycemic variability and DEB (e.g., binge eating behavior) or cognitive dysfunction could unravel the importance of insulin resistance, even in T1D. This is especially critical since “Double Diabetes” (i.e., PWT1D displaying insulin resistance) prevalence is estimated at 30–50% of PWT1D and keeps on rising [29–31]. These data highlight the significance of this trend and the need to take into account insulin resistance as a potential mediator.

### Study Aim

We aim to better understand the impact of glycemic variability in DEB and cognitive impairment, and its consequences on self-management skills in PWT1D. The primary objective of this study (the Sugar Swing Study) is to compare cognitive function, DEB, and self-management skills in PWT1D with a high glucose variability (i.e., a coefficient of variation [CV] > 36% over a 10-day of CGMS) versus those with a low glucose variability (i.e., CV < 36% [32]). Secondary objectives are: 1) to explore the associations between cognitive impairment, DEB, and self-management skills with other CGMS parameters (glucose variability as continuous variable, % glucose time in range, time below or above range, mean amplitude of glycemic excursions, standard deviation), adiposity (BMI, waist circumference), and insulin resistance markers (estimated Glucose Disposal Rate, eGDR); 2) to determine the potential role of cognitive dysfunction, interoception awareness level and insulin resistance in the relationship between glucose variability and DEB; and 3) to further our understanding of the PWT1D experience and factors impacting glycemic self-management, throughout patient’s perspectives, using a qualitative design.

We hypothesize that, among PWT1D: 1) higher glycemic variability is associated with higher DEB and poorer cognitive function, and that differences exist between sexes; 2) higher DEB and poorer cognitive function are associated with lower self-management skills; and 3) cognitive impairment, interoception awareness and insulin resistance may mediate the relationship between glycemic variability and DEB.

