Glycemic value before and after each session will be collected from CGMS (if participants are experiencing or have experienced hypoglycemia within the last hour, they will be asked to postpone the session) and participants will be asked to perform each session in the same condition (i.e., time of day, location, computers). ***Session A:*** Eating behavior will be assessed by the *Eating Disorder Examination Questionnaire* (a 36-item questionnaire to measure of the range and the severity of eating disorder feature over the past four weeks [38]) and by the *Binge Eating Scale* (a 16-item questionnaire assessing the severity of binge eating behavior [39]). During this session, cognitive flexibility will be assessed by the *Detail and Flexibility Questionnaire* (a 24-item questionnaire validated in eating disorder and exploring difficulties in flexibility/cognitive rigidity and attention to detail/weak central coherence [40]). Attention will be measured by the *Category Switch Task* (a test of divided attention with two simple categorization tasks [41]) and attention Deficit Hyperactive Disorder will be screened by the *Adult ADHD Self-Report Scale* (6 items) [42]. ***Session B:*** The level of interoception will be assessed by the *Multidimensional Assessment of Interoceptive Awareness version 2* (a 32-item questionnaire to measure the conscious level of interoception’s multiple dimensions [43]). This session will also include 3 neurocognitive tasks: the *Tower of London task* (an assessment of executive functioning with a focus on planning abilities [44]), the *Stop Signal Task* (an assessment of impulsivity through the time needed to inhibit a prepotent response [45]), and the *5-Trial Adjusting Delay Discounting* (a quick procedure to estimate delay discount rates of monetary rewards [46]). ***Session C:*** During this session, we will conduct an *Emotional Go/No-Go Task* (a measure of inhibition leverages by emotion recognition and regulation [47]) and the *Attentional Cueing Procedure* (a conditional learning paradigm to study the effects of threat stimuli on capturing and holding attention). Behavioral impulsivity will be measured by the *Short UPPS-P Impulsive Behavior Scale* (a 20-item self-report questionnaire assessing impulsivity as a multifaceted construct [48]). Susceptibility to food reward will be estimated using the *modified Yale Food Addiction Scale 2.0* (a 13-item questionnaire assessing food addiction [49]).

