### Statistical analysis

The sociodemographic characteristics and health outcomes of individuals in the study sample will be summarized with descriptive statistics. Groups will be compared across CV statuses by using the χ2 test for categorical variables and the unpaired *t*-test for continuous variables, or nonparametric equivalent, as appropriate. ANCOVA and generalized linear models will be used to consider potential confounding factors (i.e., sex, BMI, diabetes duration, age of onset, presence of macro- or microvascular complications). Moderation-Mediation analysis will be conducted (PROCESS Macro; Fig. 2). Data curation and preprocessing will be an important part of the statistical plan. To ensure their comparability and interpretability, data will be standardized, or scaling featured, using Scikit-Learn 0.24.2 (a python library). Then artificial intelligence approaches (i.e., LASSO regression or neuronal networks) will be used to explore the potential best predictors of DEB and self-management skills.

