### Sample size

The sample size has been estimated based on the cognitive flexibility (one of the most relevant cognitive functions for both disordered eating and self-management skills) effect size computed by Brands et al. [52] in their meta-analysis (*d* = -0.54, SD = 1.07; α = 0.05). Given the potential failure per protocol observed in a similar study design [53], we increased the estimated sample size by 20%. The total number of participants to recruit is established at 150 (75 per group). As an n > 100 is minimally recommended for Least Absolute Shrinkage and Selection Operator, (LASSO) regression, this sample size will also fit for more complex statistical procedures.

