## Discussion

This project is groundbreaking in its methodological framework: its use of CGMS and its combination of objective and subjective assessment tools. Moreover, this creative design differs from the current literature in that we start from a biological parameter to identify associated behaviors (whereas most of the studies split the groups into DEB—no DEB). The use of a mixed-method design is also a critical advance. Indeed, the current literature struggles to highlight objective quantitative differences, whereas subjective assessments of PWT1D highlight the importance of cognitive impairment. We believe that we can better understand these discrepancies with this combined approach.

Advances in the web-based infrastructure for research procedures and tools virtualization resulting from experience gained during the COVID pandemic offer us a unique opportunity. Indeed, one of the novel aspects brought by this study is that it can be conducted entirely from home (i.e., online). This is particularly relevant for the second-largest country in the world, which raises the important issue of the inclusiveness of participants living in distant parts of Canada. Therefore, this study will demonstrate the applicability of these new research methods to develop more inclusive studies in the future, especially for territorial disparities.

A better comprehension of the mechanisms and impact of cognitive impairment, especially on DEB and glycemic variability, will result in their earlier detection. This may lead to specific cognitive remediation training, more appropriate communication materials, and thus strengthen patients’ self-management skills. Confirmation of our hypotheses will allow us to study the impact of interventions aimed at reducing glycemic variability (e.g., semi-closed or closed loop system, low carb diet) on brain complications and eating behaviors in PWT1D.

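### The primary objective spans three domains and about 10 to 14 instruments with no named primary endpoint, while the sample size covers one comparison of cognitive flexibility

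*Protocol article*

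**What the plan says.** All references are to the protocol article.

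- **Study Aim:** "The primary objective of this study (the Sugar Swing Study) is to compare cognitive function, DEB, and self-management skills in PWT1D". The contrast is between participants with a glucose coefficient of variation (CV) above 36% and those below it. Neither this section nor any other singles out an instrument or score.
- **Inclusion visit; Eating behavior and cognitive tasks:** these sections list the instruments. For the construct used in sizing, the text is "cognitive flexibility will be assessed by the *Detail and Flexibility Questionnaire", a self-report questionnaire. The Category Switch Task appears separately, as a measure of attention.
- **Sample size:** "The sample size has been estimated based on the cognitive flexibility" effect taken from a meta-analysis. The inputs are a difference of 0.54 in absolute value with "SD = 1.07; α = 0.05", followed by a 20% increase. The result is "The total number of participants to recruit is established at 150 (75 per group"). Cognitive flexibility is described as one of the most relevant functions, but is not called the primary endpoint.
- **Statistical analysis:** "Groups will be compared across CV statuses by using the χ2 test for categorical variables" and by t-test or a nonparametric equivalent for continuous ones. No order of testing is given.

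**The concern.** A primary objective and a sample size calculation should refer to the same comparison. Here one refers to three whole domains and the other to a single construct within one of them. The plan does not say which result decides whether the primary objective has been met. If it were followed as written, many group comparisons would bear on one primary claim.

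Two things are at stake. First, the 0.05 used for sizing is the error rate of one test. It would not be the error rate of a claim that can draw on many. Second, the power of the study applies to one outcome. Conclusions about disordered eating or self-management, or an adjustment for multiple testing added later, are not covered by the calculation.

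**Working it through.** **1. Reproduce the planned size.** Inputs from the Sample size section: difference 0.54, SD 1.07, alpha 0.05, inflation by 20%. Two-sidedness and 80% power are not stated and are assumed here.

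n per group = 2 × (1.960 + 0.842)² × (1.07 / 0.54)² = 2 × 7.849 × 3.926 = 61.6, rounded up to 62.

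62 × 1.2 = 74.4, rounded up to 75 per group, 150 in total. This matches the plan. Reading 0.54 as a standardised difference (SD 1) with 85% power also gives 62 and 75. On either reading the figure corresponds to one comparison.

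**2. Count the instruments in the primary objective.** The document supports more than one mapping.

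| Domain | Wider mapping | Narrower mapping |
|---|---|---|
| Cognitive function | 9: six tasks plus the flexibility, ADHD and UPPS-P questionnaires | 6: tasks only |
| Disordered eating | 3: EDE-Q, Binge Eating Scale, food addiction scale | 2: EDE-Q, Binge Eating Scale |
| Self-management | 2: Diabetes Behavior Rating Scale, Type 1 Distress Scale | 2 |
| Total | 14 | 10 |

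Both counts leave out interoception (a mediator), anxiety, depression and numeracy. The narrower mapping follows the abstract, which lists flexibility, attention deficit and impulsivity under self-report questionnaires and names the measured cognitive functions separately. It also follows the description of the food addiction scale as a measure of food reward. On that mapping the one instrument assigned to the sized construct falls outside the cognitive count.

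**3. Chance of at least one false positive, if each test were run at 0.05.** For k independent tests this is 1 − 0.95^k.

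- k = 14: 1 − 0.95^14 = 51%
- k = 10: 1 − 0.95^10 = 40%
- k = 3 (one test per domain): 1 − 0.95^3 = 14%

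With correlated results (equicorrelated normal statistics, 400,000 simulated draws):

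| Correlation | 14 tests | 3 tests |
|---|---|---|
| 0.2 | 47% | 14% |
| 0.3 | 44% | 14% |
| 0.5 | 35% | 12% |
| 0.7 | 25% | 11% |
| 0.8 | 20% | 10% |

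**4. Cost of Bonferroni adjustment without re-sizing.** With 62 evaluable per group, the standard error is 1.07 × √(2/62) = 0.192 and the expected statistic is 0.54 / 0.192 = 2.81. Power is Φ(2.81 − z), where z is the two-sided critical value.

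- Alpha 0.05, z = 1.960: 80%
- Alpha 0.05/3 = 0.0167, z = 2.394: 66%
- Alpha 0.05/14 = 0.0036, z = 2.914: 46%

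Keeping 80% power under Bonferroni would need 83 per group for 3 tests (200 in total after the factor of 1.2), or 111 per group for 14 tests (267 in total).

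**The case against.** The strongest reply is that this is a condensed article about an observational study that aims at understanding. Multiplicity rules and the choice of scores within an instrument commonly sit in an analysis plan, which is not shown. That stands as far as it goes: the absence of an adjustment method is not the point made here. The mismatch lies between two statements that are both shown, the objective and the sample size.

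A reader might infer several stronger things, and the document does not support them:

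- **That every instrument is to be tested at 0.05.** Alpha appears only in the Sample size section. The Statistical analysis section gives test types and no level, so the error rates above are conditional.
- **That a false positive is more likely than not.** Only 14 independent tests exceed 50%. These scales overlap and are given to the same people, so independence is implausible.
- **That any single positive result would count as success.** No decision rule is stated in either direction.
- **That sex-specific tests add to the primary family.** Sex enters as a covariate and a moderator; no sex-specific primary comparison is stated.
- **That the study's own flexibility questionnaire and switching task will disagree.** The Discussion says "the current literature struggles to highlight objective quantitative differences, whereas subjective assessments of PWT1D highlight the importance of cognitive impairment", but this describes published work and supports the mixed-method design.

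The reply that flexibility already has an assigned instrument is also correct. It settles the measure of that construct, but does not make it the primary endpoint.

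**Conclusion.** The point holds. The primary objective covers three domains and about 10 to 14 instruments, no primary endpoint is named, and the sample size supports one comparison of cognitive flexibility. If each instrument were tested at 0.05, the chance of at least one false positive would be about 20% to 51% for 14 tests, four to ten times the nominal level. It would be 40% for 10 independent tests and no more than about 14% for one test per domain.

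These figures assume unadjusted two-sided tests and, for the lower end of the 14-test range, a common correlation of 0.8. The power figures assume 80% planned power, the stated SD of 1.07 and 62 evaluable participants per group. The mismatch itself depends on none of these assumptions, because it can be read directly from the two sections.

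**What to change.** Name one prespecified score of cognitive flexibility, the sized construct, as the primary endpoint, tested at 0.05. The section on eating behavior and cognitive tasks assigns this construct to the Detail and Flexibility Questionnaire, so a score from it is the consistent choice. If a task score is preferred, amend that section to match and confirm that the assumed effect applies to the task.

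Then test one disordered-eating score and one self-management score in a fixed order, each at 0.05 and only if the preceding test is significant. Report all remaining measures as secondary or exploratory with false-discovery-rate control. Make the change before outcomes are compared by CV group.

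The cost is wording in the Study Aim and Statistical analysis sections and weaker claims for the non-primary measures. Power for the primary endpoint and N = 150 are unchanged.

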#### Glucose variability and insulin resistance

CGMS will be performed over a 10-day period using a Dexcom G6 and data reported following the international consensus [35, 36]. Required material and assistance will be provided by mail if needed. In the province of Quebec (Canada) both the Freestyle Libre and Dexcom are eligible for reimbursement by the public insurance plan for most PWT1D. For the few patients who would not have access to CGMS yet, we will provide the equipment for the duration of the study and a set of sensors will be sent to all participants, as a courtesy for participating in the study. Glucose Management Indicator (GMI) will be used to estimate A1C from CGMS during the study time. The estimated Glucose Disposal Rate (eGDR) will be computed (eGDR is a validated tool for estimating insulin sensitivity in T1D; eGDR = 21.158 + -0.09 × waist circumference − 3.407 × hypertension [defined as 0 = no, 1 = yes] − 0.551 × HbA1c). During the period of CGMS recording, PWT1D will be invited to track their dietary intakes using image-assisted food tracking mobile application over 2 days at random (one weekday and one weekend day) with the Keenoa® application [37].

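### Glucose SD and MAGE rise with mean glucose, and the stated covariates include no glucose-level term, so their associations with the outcomes could not be told apart from average glycemia

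*Protocol article*

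**What the plan says.** The primary exposure is a split on CV, with high variability defined as "a coefficient of variation [CV] > 36% over a 10-day of CGMS" (Study Aim). Secondary objective 1 in the same section plans "to explore the associations between cognitive impairment, DEB, and self-management skills with other CGMS parameters", and lists, besides continuous glucose variability, "glucose time in range, time below or above range, mean amplitude of glycemic excursions, standard deviation". Mean glucose is not in that list.

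The Statistical analysis section says that ANCOVA and generalized linear models will take account of "potential confounding factors (i.e., sex, BMI, diabetes duration, age of onset, presence of macro- or microvascular complications". No mean glucose, GMI or HbA1c appears there.

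The Background explains that mechanisms of cognitive impairment are hard to characterize, "partly due to numerous confounding factors (e.g., age, HbA1c level, psychiatric comorbidities". It adds: "Chronic hyperglycemia, longer diabetes duration, and the presence of micro- and macrovascular complications have all been associated with a higher risk of cognitive impairment".

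Glucose level is measured. In the section on glucose variability and insulin resistance, "Glucose Management Indicator (GMI) will be used to estimate A1C from CGMS during the study time". The last available HbA1c, up to 6 months old, is taken at the inclusion visit. Neither is given a role as covariate in the association models.

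**The concern.** The study's rationale contrasts long-term glucose level, as captured by HbA1c, with fluctuation around that level. SD and MAGE mix the two. A participant with a high mean and an ordinary CV has a large SD. If level alone affects an outcome, SD and MAGE will tend to show an association with it even though swings play no part. With no level term in the model, the reader of such a result could not say which of the two it reflects. For cognition, the document itself supplies the competing explanation and then leaves it out of the adjustment set.

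**Working it through.** The plan states no figure on this point, so there is none to reproduce. Every distribution input below is an assumption.

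**Inputs (assumed).** n = 125, which is 150 / 1.2, the recruitment target before its 20% increase. Mean glucose 9.2 (between-person SD 1.5) mmol/L. CV 36 (SD 5.5)%. The outcome depends on mean glucose only. MAGE is assumed to follow SD.

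**Step 1, the identity.** CV = SD / mean, so SD = CV × mean. Take two participants, both with CV 36%, one between-person SD either side of the average mean:
- mean 7.7: SD = 0.36 × 7.7 = 2.77 mmol/L
- mean 10.7: SD = 0.36 × 10.7 = 3.85 mmol/L

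The second has an SD 3.85 / 2.77 = 1.39 times as large at the same relative variability.

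**Step 2, correlation of SD with the mean.** The relative spreads are 1.5 / 9.2 = 0.163 and 5.5 / 36 = 0.153. If CV is independent of the mean, r = 0.163 / √(0.163² + 0.153² + 0.163² × 0.153²) = 0.163 / 0.225 = 0.72. Simulation also gives 0.72.

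**Step 3, false-positive rate by formula.** The induced correlation of SD with the outcome is 0.72 times the mean–outcome correlation. The Fisher transform is multiplied by √(125 − 3) = 11.05 and compared with 1.96.
- 0.3: 0.216, z = 2.42, rate Φ(0.46) = 0.68
- 0.2: 0.144, z = 1.60, rate Φ(−0.36) = 0.36
- 0.1: 0.072, z = 0.80, rate Φ(−1.16) = 0.12

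**Step 4, simulation (1,500 replicates per setting).** Share of studies with p < 0.05 and no true variability effect:

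| Mean–CV correlation | Mean–outcome correlation | SD | MAGE | Either, mean added |
|---|---|---|---|---|
| −0.3 | 0.2 | 0.29 | 0.24 | 0.04–0.05 |
| −0.3 | 0.3 | 0.55 | 0.50 | 0.04–0.05 |
| 0 | 0.2 | 0.39 | 0.35 | 0.04–0.05 |
| 0 | 0.3 | 0.68 | 0.64 | 0.04–0.05 |
| 0.3 | 0.2 | 0.46 | 0.43 | 0.04–0.05 |
| 0.3 | 0.3 | 0.81 | 0.77 | 0.04–0.05 |

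A repeat with the same n gave 29 to 79% for SD and 24 to 71% for MAGE. With a mean–outcome correlation of 0.1 the unadjusted rate is about 10 to 15%.

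**Step 5, other assumed spreads.** With between-person variation of 15–25% in the mean and 12–20% in CV, mean–CV correlation −0.2 to 0.2 and n = 120 or 150, SD correlates 0.62 to 0.92 with the mean. Unadjusted SD is falsely significant in 29–63% of runs at a mean–outcome correlation of 0.2, and in 52–94% at 0.3. Adding mean glucose gives 3–7%. Adding only an HbA1c-type proxy (correlation 0.85 with the mean) leaves 6–35%. MAGE was not run in this set.

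**Step 6, CV for comparison.** In the settings of step 5, unadjusted CV is falsely significant in 4–14% of runs, and in about 5% when CV is uncorrelated with the mean. At mean–CV and mean–outcome correlations both of 0.3, the induced correlation is 0.09, z = 0.09 × 11.05 = 0.99, and the rate is Φ(−0.97) = 0.17. CV is largely but not wholly spared.

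**The case against.** A reader might infer that the study will report SD and MAGE as effects of variability. The text does not support that. They are called other CGMS parameters, sit beside time-in-range measures that follow glucose level, and are only to be explored. A reader might also infer that the study cannot separate level from variability at all. That is wrong: CV, both as the primary split and as a continuous variable, is already divided by the mean, and GMI, HbA1c and time above range are all obtained. An SD result that CV contradicted would be visible in the same results.

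Further points stand in part:
- The confounder list may not be exhaustive. The Background treats diabetes numeracy, and the inclusion-visit section treats psychotropic drugs, as potential confounders, and neither is in the list. Even so, nowhere is a glucose-level covariate stated, and the list that is stated does not serve these two exposures.
- The quoted link to chronic hyperglycemia concerns cognition only. For eating, the Background describes hyperglycemia as suppressing hunger, so bias through the mean need not favor the hypothesis.
- Mean glucose may be a consequence. The Background says that insulin omission raises HbA1c and that cognitive impairment may worsen glycemic levels through poorer self-management. Conditioning on a consequence can itself bias an estimate. When the outcome drives mean glucose and CV is independent of the mean, adjusted SD still rejects at about 5%, but other structures were not tested. It would be too strong to call an association variability only if it survives adjustment.
- The magnitudes rest wholly on assumptions. The Background calls observed cognitive effects weak to mild, and the simulated models contain none of the planned covariates.

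**Conclusion.** The point holds in a limited form. In secondary objective 1, with the covariates as stated, an association of SD or MAGE with an outcome could not be distinguished from an effect of average glycemia. The identity SD = CV × mean needs no assumption; the size of the distortion does. It is about 29–80% false positives for SD and 24–77% for MAGE at mean–outcome correlations of 0.2 to 0.3, and about 10–15% at 0.1, against about 5% with mean glucose in the model. The primary comparison and the continuous CV analysis are largely unaffected, and the objective is exploratory. The change is worth making because it settles what the SD and MAGE results can support and uses data already collected.

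**What to change.** Add to the Statistical analysis section, for secondary objective 1:
- Report each SD and MAGE model both without and with 10-day mean glucose (or GMI) from the same CGMS recording as a covariate. An HbA1c up to 6 months old is not an adequate substitute.
- Describe the unadjusted association as reflecting overall glycemia plus variability.
- Base any statement about variability on the adjusted estimate or on CV, and note that mean glucose may itself be a consequence of DEB or self-management.
- Do not enter CV, SD and mean glucose together, since SD is the product of the other two.

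The cost is a few sentences, one covariate already recorded, and wider standard errors. At an SD–mean correlation of 0.72 the standard error grows by a factor of about 1 / √(1 − 0.72²) = 1.44, ignoring any gain from explained outcome variance. At 0.62 the factor is 1.27, and at 0.92 it is 2.55. The sample size and the primary comparison do not change.
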